5.0 PHARMACOLOGY CONSENSUS ASSAY METHODOLOGY LINKS

- Pharmacology Tutorial “ACTG Pharmacology Study Conduct: Impact on PK-PD Analysis”:

<https://www.actgnetwork.org/lab_resources/pharm/index.aspx>

- Pharmacology Sample Processing Guidelines:

<https://www.actgnetwork.org/members/download/other/Standard-PLASMA-Pharmacology-Sampling.doc>

6.0 SHIPPING CONSENSUS METHODOLOGY LINKS

- Guidelines for Shipping Diagnostic Specimens:

<https://www.actgnetwork.org/pub/download/labmanual/22-ALM-Diagnostic-Shipping-Guidelines.pdf>

- ACTG Specimen Repository (BRI) Shipping Guidelines:

<https://www.actgnetwork.org/lab_resources/specimen_repository.aspx>

- Outsourcing Laboratories (JHU) Shipping Instructions:

<https://www.actgnetwork.org/lab_resources/hiv_rna.aspx>

1. CLINICAL CONSIDERATIONS
   1. Pharmacokinetic Studies

Blood samples should be kept on ice until processed. Each blood sample should be processed, and the plasma separated by centrifugation, within 90 minutes of the time of collection. Centrifuge the blood sample at 800 x g for 10 minutes to obtain the plasma. Transfer the plasma to a pre-labeled polypropylene cryovial that has a screw top. The plasma should be kept in an ice bath until it is frozen. Freeze the cryovials in the upright position and maintain frozen at -20˚C to -70˚C until shipment.

# APPENDIX III: A5249s SPECIMEN COLLECTION, PROCESSING, AND SHIPMENT

1.0 OVERVIEW

All specimens will be collected per Section 6.0, Clinical and Laboratory Evaluations. Collection, processing, and shipment details for select specimens are below. For instructions regarding specimens not listed on this table, please refer to the LPC. All specimens generated from this protocol must be labeled, stored, and shipped according to the LDMS guidelines unless otherwise specified.

1. TABLE

| Assay/Procedure | Tube Type or Specimen Type and Quantity | Derivative | Processing Instructions | Aliquots | Shipping Instructions |
| --- | --- | --- | --- | --- | --- |
| VIROLOGY |  |  |  |  |  |
| Plasma HIV-1 RNA | 1 x 6-ml whole blood EDTA (purple top) tube, according to the schedule of events in section 6.0 | Plasma | Follow ACTG guidelines for processing | Prepare at least 2 x 1 mL  Preparation of additional aliquots is strongly encouraged.  Store on site at -70°C  LDMS code: BLD/EDT/PL2 | Ship two (2) 1 ml aliquots from visit days 1 through 7 to the Johns Hopkins University for viral load analysis. Ship remaining aliquots according to current BRI guidelines. |

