1. HYPOTHESIS AND STUDY OBJECTIVE
   1. Hypothesis

In treatment-naïve subjects starting a potent ARV regimen consisting of RAL and FTC/TDF, plasma HIV-1 RNA levels will show measurable decline within the first 12-18 hours after treatment initiation, and possibly earlier.

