6.0 EVALUATIONS

6.1 Schedule of Events

| Evaluation | Screen-ing | Pre-entry | Entry Evaluations | | | | | | Post-Entry Evaluations | | | | | | | | | |
| --- | --- | --- | --- | --- | --- | --- | --- | --- | --- | --- | --- | --- | --- | --- | --- | --- | --- | --- |
| Day |  |  | 0 | | | | | | 1 | | | | | 2 | | 3 | 4 | 7 |
| Week |  |  | 1 | | | | | | 1 | | | | | 1 | | 1 | 1 | 1 |
|  |  |  | Sample time, relative to first dose of study drug and allowed window | | | | | | | | | | | | | | | |
|  |  |  | 0h (pre-dose) | 2h (±30 min) | 4h | 6h | | 12h | | 18h | 24h | 30h | 36h | 42h | Day2 | Day3 | Day4 | Day7 |
| HIV-1 RNA Plasma Sample | X | X | X | X | X | X | | X | | X | X | X | X | X | X | X | X | X |
| Dose Administered in Clinic/GCRC |  |  | X |  |  |  | | X | |  | X |  |  |  | X | X | X | X |
| Medication Diary1 |  |  |  |  |  |  | |  | |  |  |  |  |  | D | C,D | C,D | C |
| Example, first dose of study drug given Monday at 9:00 | | | Monday | | | | | | | Tuesday | | | | Wednesday | | Thursday | Friday | Monday |
| 8:55 | 11:00 | 13:00 | | 15:00 | 21:00 | | 3:00 | 9:00 | 15:00 | 21:00 | 3:00 | 9:00 | 9:00 | 9:00 | 9:00 |

1D=distributed, C=collected.

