6.2.2 Pre-entry, Entry, and Post-Entry

- - - 1. HIV-1 RNA results from samples drawn for the A5248 study visits at pre-entry, entry (day 0 pre-dose), day 2, and day 7 will be used for this substudy.

NOTE: A separate tracking form will be used for HIV-1 RNA samples

taken from substudy subjects at pre-entry, entry (day 0 pre-dose), day 2, and day 7.

- - - 1. After starting study medications, samples will be obtained as part of this substudy as per the Schedule of Events. Subjects will be required to stay overnight in the hospital/GCRC from Day 0 to Day 2. On days 2, 3, 4, and 7, the morning study medication dose will be taken in the clinic.
      2. Medication diaries will be given to subjects on day 2 with instructions to record the times they take their study medications through day 7 of the study. Subjects will bring their medication diaries to their study visits on days 3, 4, and 7 for review.

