1. STATISTICAL CONSIDERATIONS

In a subset of A5248 subjects, intensive measurement of plasma HIV-1 RNA over the first few days following treatment initiation will be conducted. In addition to sample times of the parent study, plasma samples for quantification of HIV-1 RNA will be collected as per the Schedule of Events. Intensive sampling will allow precise estimation of the time that plasma HIV-1 RNA begins to decline following initiation of the integrase-inhibitor-based regimen. The hypothesis is that this “shoulder” will be of shorter duration than that of regimens without an integrase inhibitor. The primary analysis will be AT, retaining only those subjects who continue to take all medications in the regimen as prescribed through day 7. Subjects who discontinue or modify the RAL and FTC/TDF regimen prior to day 7 will be replaced in accrual to the substudy. Data from these subjects may be retained for secondary ITT analyses.

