1. TABLE

| Assay/Procedure | Tube Type or Specimen Type and Quantity | Derivative | Processing Instructions | Aliquots | Shipping Instructions |
| --- | --- | --- | --- | --- | --- |
| VIROLOGY |  |  |  |  |  |
| Plasma HIV-1 RNA (batched and real time) | 1 x 6-mL whole blood EDTA (purple top) tube, according to the Schedule of Events in section 6.0 | Plasma | Follow ACTG guidelines for processing. | 2 x 1 mL plasma  Store on site at -70°C  LDMS code:  BLD/EDT/PL2 | Batch and ship samples from entry through day 21 to Johns Hopkins University when instructed by the team.  Ship 2 x 1 mL aliquots at all other timepoints real time to Johns Hopkins University. |
| HIV-1 RNA Single Copy Assay (batched) | 2 x 10-mL whole blood EDTA (purple top) tube at entry, and Days 2 and 7  3 x 10-mL whole blood EDTA (purple top) tube at Days 10 and 14  3 x 10-mL and 1 x 5-mL (35 mL total) whole blood EDTA (purple top) tube at Days 21, 28, and 56  5 x 10-mL whole blood EDTA (purple top) tube at Weeks 12, 16, 20, 24, 36, 48, 60, and 72/final visit | Plasma | **Process within 4 hours.**  Spin blood at 400 x g for 10 minutes in a table top centrifuge. Remove plasma very carefully without disturbing the buffy coat and/or mixing cells into the plasma.  IMPORTANT: **To prevent contamination of the plasma with cells, leave about 0.5 mL of plasma behind on top of cells.**    Re-spin plasma at 1350 x g for 15 min. Again leave about 0.5mL of plasma behind to prevent cell contamination. Save this last 0.5mL in a separate cryovial for 16s DNA testing. If cells are inadvertently mixed with the plasma, re-spin the sample and remove the plasma without disturbing the cells.  NOTE: When a sample is processed for the single copy assay, a sufficient layer of plasma must be left behind to ensure that absolutely no cells in the buffy coat or red blood cell layers are removed with the plasma. | Collect a minimum of 5 x 1.5 mL plasma aliquots at Days 2 and 7 and 10 x 1.5 mL plasma aliquots at all other timepoints  LDMS code:  BLD/EDT/PL2 | Ship according to current BRI guidelines. |

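### Appendix III sends only day 1 to 7 substudy samples for viral load assay, so the 2, 4, 6 and 12 h samples of day 0, which cover the hypothesised onset window, have no instruction to be assayed

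*Protocol*

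**What the plan says.** **Objective and hypothesis (Appendix I, 1.1 and 1.2).** The only objective is to estimate when first-phase decay begins. The hypothesis is that "plasma HIV-1 RNA levels will show measurable decline within the first 12-18 hours after treatment initiation, and possibly earlier".

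**Schedule (Appendix I, 6.1).** The HIV-1 RNA row is marked at every time, beginning "0h (pre-dose) | 2h (±30 min) | 4h | 6h" and continuing with 12, 18, 24, 30, 36 and 42 h and days 2, 3, 4 and 7. The clock row ("Example, first dose of study drug given Monday at 9:00") puts the 12 h draw at 21:00 on Monday, which is day 0, and the 18 h draw at 3:00 on Tuesday, which is day 1.

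**Purpose of the samples (Appendix I, Statistical Considerations).** Beyond the parent study's sample times, "plasma samples for quantification of HIV-1 RNA will be collected as per the Schedule of Events".

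**Shipping of substudy samples (Appendix III, table).** "Ship two (2) 1 ml aliquots from visit days 1 through 7 to the Johns Hopkins University for viral load analysis", followed by "Ship remaining aliquots according to current BRI guidelines".

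**What the main study supplies (Appendix I, 6.2.2).** The substudy uses "HIV-1 RNA results from samples drawn for the A5248 study visits at pre-entry, entry (day 0 pre-dose), day 2, and day 7". Other post-dose samples are the substudy's own.

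**Shipping of main-study samples (Appendix II, table).** "Batch and ship samples from entry through day 21 to Johns Hopkins University when instructed by the team".

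**The concern.** The shipping rule starts at day 1, while the sampling that sets this substudy apart starts on day 0. Of the nine post-dose draws in the first 42 h, the four earliest (2, 4, 6 and 12 h) fall outside the rule. They cover the stretch in which the hypothesis places the onset, or lead directly up to it.

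Two planned analyses depend on them (Appendix I, 9.2): reading the length of the flat shoulder from the graphs, and a broken-line mixed model with a profile likelihood over the transition time. Subjects spend two nights in hospital so that these samples can be taken.

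**Working it through.** **1. Does another rule cover the four samples?**
- Appendix II governs the main-study draws. The main-study schedule has one entry draw, which 6.2.2 identifies as the day 0 pre-dose sample. The 0 h value is therefore assayed; the 2-12 h values are not covered.
- Appendix I, 6.3.2 refers substudy samples to Appendix III.
- The Appendix III overview defers to the Laboratory Processing Chart only for specimens not in its table. Plasma HIV-1 RNA is in the table.

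Under the literal rule the assayed times are pre-entry, 0, 18, 24, 30, 36 and 42 h, and days 2, 3, 4 and 7. In the extracted schedule the 12 h cell straddles the day 0/day 1 header. If it is counted as day 1 despite the clock row, the first post-dose value is at 12 h and the 2, 4 and 6 h samples are still left out.

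**2. The substudy's own precision figure (Appendix I, 9.1).** Half-width = t(0.975, n-1) x CV / √n. For n = 10 and CV 24%: 2.262 x 0.24 / 3.162 = 17.2% of the mean. At a mean of 0.5 day this is 0.086 day, or 2.06 h, which matches the stated 17%, 0.09 day and 2 hours. The plan thus expects about ±2 h around 12 h, while the literal rule leaves an 18 h gap.

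**3. Early slope estimated.** The 9.2 model has an intercept, an early slope and a later slope. Take baseline as one point at hour zero. For any transition time between 0 and 18 h, the later line is fixed by the values from 18 h on, and the early slope adjusts to join it to baseline. Every such transition time gives the same fitted values. Numerically, the residual sum of squares changed by a relative 1e-14 or less over 0.5 to 18 h, so the profile likelihood is flat there.

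A simulation (10 subjects, 400 runs, mean onset 12 h, CV 24%, d1 = 0.80/day, samples through day 7) gave these SDs of the estimated onset:

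| Residual SD (log10, assumed) | Full schedule | Literal rule |
|---|---|---|
| 0.05 | 2.3 h | 7.1 h |
| 0.10 | 5.3 h | 9.2 h |
| 0.20 | 9.2 h | 12.0 h |

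The literal-rule SDs are only indicative, because the position chosen within a flat stretch is arbitrary.

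**4. Early slope fixed at zero (the lenient case).** Onset is where the later line, extended back, meets the flat level:

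Var(onset) = (σ/s)² x [1/n₀ + 1/m + (t̄ - τ)²/Sxx]

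- s = 0.80 / ln 10 = 0.347 log10/day (d1 = 0.80 from main protocol 9.4)
- τ = 0.5 day; σ = 0.10 log10 (assumed; the protocol gives none), so σ/s = 0.288 day
- Points after the break: 18, 24, 30, 36, 42 and 48 h, days 3 and 4. So m = 8, t̄ = 1.906, Sxx = 8.367, and the last two terms sum to 0.125 + 0.236 = 0.361
- n₀ counts values on the flat part: 6 in full (pre-entry, 0, 2, 4, 6, 12 h), 2 under the literal rule

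Full: 0.288 x √(0.167 + 0.361) = 0.209 day. Literal: 0.288 x √(0.500 + 0.361) = 0.267 day. Variance ratio: 0.861 / 0.528 = 1.63. With 12 h assayed (n₀ = 3) it is 0.695 / 0.528 = 1.32.

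**5. Adding between-subject variation.** CV 24% of 0.5 day is 0.12 day, variance 0.0144.

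| σ | Full | Literal | Ratio | 10 subjects are worth |
|---|---|---|---|---|
| 0.05 | 0.0109 + 0.0144 | 0.0178 + 0.0144 | 1.27 | 7.9 |
| 0.10 | 0.0437 + 0.0144 | 0.0713 + 0.0144 | 1.47 | 6.8 |
| 0.20 | 0.1750 + 0.0144 | 0.2854 + 0.0144 | 1.58 | 6.3 |

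**6. Sensitivity of the within-subject ratio.** With onset at 18 h (the 18 h value then lies on the flat part) it is (1/3 + 0.398) / (1/7 + 0.398) = 1.35. At 24 h it is (1/4 + 0.451) / (1/8 + 0.451) = 1.22. At σ = 0.10 with step 5 added, these make 10 subjects worth about 7.9 and 8.6. The easing begins only once onset reaches 18 h; just below, the ratio is (1/2 + 0.285) / (1/6 + 0.285) = 1.74. Adding day 7 at onset 0.5 day raises it to (1/2 + 0.235) / (1/6 + 0.235) = 1.83.

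**The case against.** The strongest reply is that nothing in the substudy design chooses to leave these samples untested. The schedule, the design section and the statistical section all treat every draw as an HIV-1 RNA measurement, and one table cell is misworded. That stands: this is an internal inconsistency, probably a slip.

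A second reply is that nothing need be lost. At least two 1 mL aliquots are prepared per draw and stored at -70°C, so a missed shipment can be made good before analysis. That also stands. A reader might infer that the early measurements are gone for good; the documents support only that no instruction sends them for assay.

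A third is that the instruction on remaining aliquots may mean only extras beyond the two shipped. On that reading the day 0 post-dose aliquots have no stated destination and stay on site; on the other they go to the repository. Neither reading has them assayed.

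Two stronger inferences about size are tempting. One is that onset cannot be estimated at all. Section 9.2 expects a zero early slope, and if that is imposed, onset is still estimable, less precisely. The other is to turn the 1.63 ratio directly into 10 subjects shrinking to about 6, whatever the residual SD. That ignores between-subject variation, on which the substudy's sample size rests. With it, the equivalent does depend on the residual SD and is about 7 at 0.10.

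Finally, this is an optional 10-subject substudy, and the A5248 primary endpoint is untouched. That limits the reach of the error, but it still bears on the substudy's only objective.

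**Conclusion.** The point holds as a conflict between Appendix III and the substudy's schedule, hypothesis and statistical section. Read literally, the protocol provides no post-dose viral load before 18 h (before 12 h if the 12 h draw is counted as day 1). An onset before 18 h could not be seen on the graphs. It would not be identified with the early slope estimated, given a single baseline point at hour zero, and with that slope fixed at zero it would rest on back-extrapolation.

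In the zero-slope case at onset 0.5 day with samples through day 4, the cost is a within-subject SE of about 0.27 instead of 0.21 day, and an effective size of about 7 of 10 subjects (6.3 to 7.9). The loss is smaller for onset at 18 h or later and somewhat larger if day 7 is included. These figures depend on an assumed residual SD; the textual conflict does not. It should be corrected because the wrong instruction governs the samples the substudy most needs. The documents do not show a deliberate restriction or an irreversible loss.

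**What to change.** Change the Appendix III shipping instruction so that two 1 mL aliquots of every substudy post-dose sample, from day 0 (naming 2, 4, 6 and 12 h) through day 7, go to the assay laboratory. State that the remaining aliquots are those beyond these two. Ask sites and the repository to send any day 0 post-dose aliquots they hold for viral load assay before the substudy analysis starts.

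The cost is a one-line correction, a memo to sites and the repository, and the shipment and assay of samples the schedule already requires. No extra blood is drawn.

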#### VIROLOGY CONSENSUS METHODOLOGY LINKS

- ACTG Laboratory Manual:

<https://www.actgnetwork.org/lab_resources/lab_manual.aspx>

- ACTG Processing Guide Index:

<https://www.actgnetwork.org/pub/download/labmanual/12-ALM-Specimen-Processing.pdf>

1. SHIPPING CONSENSUS METHODOLOGY LINKS

- Guidelines for Shipping Diagnostic Specimens:

<https://www.actgnetwork.org/pub/download/labmanual/22-ALM-Diagnostic-Shipping-Guidelines.pdf>

- Guidelines for Shipping Infectious Substances:

<https://www.actgnetwork.org/pub/download/labmanual/20-ALM-Infectious-Shipping-Guidelines.pdf>

- ACTG Specimen Repository (BRI) Shipping Guidelines:

<https://www.actgnetwork.org/lab_resources/specimen_repository.aspx>

- Outsourcing Laboratories (JHU/Quest) Shipping Instructions:

<https://www.actgnetwork.org/lab_resources/hiv_rna.aspx>
